#### 2.4.3. Instruments

Data collection will be performed by using the following instruments:(1)General information questionnaire: Demographic and clinical characteristic data will be obtained by the general information questionnaire. Demographic characteristics will include age, sex, BMI, ethnicity, marital status, education level, average annual household income, place of residence, working conditions, medical payment method, drinking status, and smoking status. Clinical characteristics will include the duration of illness, the first time to be hospitalized for SCAD or not, the severity of angina, stent implantation or not, and the number of diseased coronary arteries.(2)Questionnaire for measuring patient views of involvement in myocardial infarction care [26]: This questionnaire was developed by Judith E, and translated by H. Shen [27]. Patient attitudes towards SDM will be measured by the patient involvement section of this scale, which consists of 6 items. The responses to each item are scored from 1 (Don’t agree at all) to 4 (Agree completely) with the total scores ranging from 6 to 24 points. A higher score indicates a more positive attitude towards SDM on the part of the patient. Cronbach’s α for the subscale is 0.82, indicating good internal consistency reliability.(3)Decision Self-Efficacy Scale (DSES) [28]: DSES was developed by Bunn et al., and translated by S.T. Wang et al. [29]. Decision self-efficacy is the “self-confidence or belief in one’s abilities in SDM”, and we will use DSES to assess the self-efficacy of participants towards SDM. The response options will be measured on the 5-point Likert scale (0 = not at all confident to 4 = very confident). On the advice of the original author, the total self-efficacy score is obtained by summing the 11 items and then multiplying them by 11/25. The total score ranges from 0 (not confident) to 100 (extremely confident). DESE demonstrated excellent reliability in the original study (Cronbach’s α = 0.899). The English version of DSES was translated into Chinese, back-translated, and cross-culturally adapted according to Brisin’s principles. The Chinese version of DSES consisted of 11 items. The content validity index of the Chinese version scale was 0.966. The Cronbach’s α coefficient was 0.918. The correlation coefficients between the scores of each item and the total score were 0.627–0.796 (all *p* < 0.01).(4)The Autonomy Preference Index (API) [30]: API was developed by Ende, and translated by Kim et al. [31]. The intention was assessed by 6 items using responses on the 5-point Likert scale (1 = “strongly disagree” to 5 = “strongly agree”). Because scoring for these items is reversed, a lower score indicates a greater intention. The internal consistency reliability of the subscale was excellent (Cronbach’s α = 0.82), and the test–retest reliability was 0.84.(5)The 9-item Shared Decision-Making Questionnaire (SDM-Q-9) [32]: SDM-Q-9 was developed by Kriston, and translated by B.H. Luo et al. [33]. The English version of SDM-Q-9 was translated into Chinese, back-translated, and cross-culturally adapted according to Brisin’s principles. The degree of the patient’s actual participation in SDM during treatment will be assessed by 9 items using answers on the 6-point Likert questionnaire ranging from 1 to 6 (“completely disagree” to “completely agree”). The SDM-Q-9 showed excellent validity and high acceptance, and internal consistency yielded a Cronbach’s α of 0.938 in the test sample. The initial author suggested that the original score × 20/9 be converted to 0–100 points for easy comparison. The total scores of 0–33, 34–66, and 67 and above indicated low, medium, and high levels of patient participation in shared decision making, respectively. Higher scores indicate a greater degree of patient participation in SDM.(6)The Multidimensional Scale of Perceived Social Support [34]: MSPSS was developed by Zimet, and translated by Kee-Lee Chou [35]. Perceived social support was measured with the MSPSS. The scale consists of 12 items (Cronbach’s α = 0.89) with answers ranging from “Completely disagree” to “Completely agree” (1 to 7). The measure assesses social support received from three subscales (4 items each)—friend subscales (Cronbach’s α = 0.95), family subscales (Cronbach’s α = 0.92), and significant other subscales (Cronbach’s α = 0.91). The general scores were calculated by adding the 12 items together (ranging from 12 to 84). A higher total score indicates higher levels of social support for patients.

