
#### 2.4.4. Data Analysis

The questionnaire will be checked by two people, and scientific statistical methods will be used for rigorous statistical analysis. The quantitative data collected through interviews will be analyzed using SPSS26.0. Descriptive statistics will be used to present all the variables (Table 1). Mann–Whitney U-tests or multi-sample rank-sum tests will be used to analyze the differences between general information and the level of participation in SDM in patients with SCAD. The variables that are statistically significant after monofactor analysis will be used as independent variables, and participation in SDM by SCAD patients will be used as the dependent variable for conducting multiple logistic regression analyses. The Spearman correlation analysis will be used to describe the correlation between the variables in the TPB model and participation in SDM by SCAD patients. Two-tailed *p*-values will be adopted, and *p* < 0.05 will be considered statistically significant.

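### The Decision Self-Efficacy Scale scoring rule prints its multiplier upside down (11/25 for 25/11), so the rule yields 0 to 19.36 and not the stated 0 to 100

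*Protocol article*

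**What the plan says.** All the scoring information for the DSES is in item (3) of section 2.4.3 (Instruments) of the protocol article:

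- **Number of items:** "The Chinese version of DSES consisted of 11 items".
- **Item coding:** responses are on a "5-point Likert scale (0 = not at all confident to 4 = very confident").
- **Scoring rule**, attributed to the scale's original author: "the total self-efficacy score is obtained by summing the 11 items and then multiplying them by 11/25".
- **Range:** "The total score ranges from 0 (not confident) to 100 (extremely confident").

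The planned uses of the score are in section 2.4.4 and Table 1. For reporting, "Descriptive statistics will be used to present all the variables (Table 1"), and row 1 of that table includes decision self-efficacy, summarised as mean ± SD or as median with quartiles. For association, "The Spearman correlation analysis will be used to describe the correlation between the variables in the TPB model and participation in SDM" by SCAD patients; row 4 of Table 1 lists decision self-efficacy here as a single dimension. No other part of the article gives a second DSES scoring rule or corrects this one.

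**The concern.** Four statements about one instrument stand side by side and cannot all be true. Item count, item coding and final range agree with one another under a simple linear rescaling. The multiplier does not fit them.

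At stake is the reported level of decision self-efficacy. A total between 0 and 19.36, set against printed anchors of 0 for no confidence and 100 for extreme confidence, would understate patients' confidence and would not be comparable with DSES results scored on the full 0 to 100 range. Because the rule is credited to the scale's original author, whoever writes the scoring syntax may copy it without checking. The level could also carry further: sections 2.5.2 and 2.5.3 say that the interview outline will be revised in the light of the survey results, and section 2.6 sets survey results beside interview themes in a joint display.

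**Working it through.** **Inputs** (all from section 2.4.3, item 3): 11 items; item scores 0 to 4; multiplier 11/25; stated total range 0 to 100.

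**Step 1. Raw sum.** Minimum 11 × 0 = 0; maximum 11 × 4 = 44.

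**Step 2. Attempt to reproduce the stated range with the stated rule.** 0 × 11/25 = 0 and 44 × 11/25 = 484/25 = 19.36. The rule gives 0 to 19.36, so the stated 0 to 100 is not reproduced.

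**Step 3. Other readings of the rule.**

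| Reading | Range |
|---|---|
| Items coded 1 to 5, sum × 11/25 | 11 × 11/25 = 4.84 to 55 × 11/25 = 24.2 |
| Item mean × 11/25 | 0 to 4 × 11/25 = 1.76 |
| Sum divided by 11/25, that is, sum × 25/11 | 0 to 100 |
| Item mean × 25 | 0 to 100 |

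None of the readings that multiply by 11/25 reaches 100. The last two rows are the same calculation, since sum × 25/11 = (sum/11) × 25.

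**Step 4. Multiplier required.** 100/44 = 2.2727 = 25/11, exactly the reciprocal of the printed fraction. Check: 44 × 25/11 = 100.

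**Step 5. Size of the error if the rule is followed literally.** Ratio of the fitting to the printed multiplier: (25/11)/(11/25) = 625/121 = 5.165, or 5.17 rounded. Example: a raw sum of 33 gives 33 × 25/11 = 75 with the fitting factor and 33 × 11/25 = 14.52 with the printed one. Means, SDs, medians and quartiles all shrink by the same constant.

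**Step 6. What the error reaches.**

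- *Descriptive summaries (Table 1, row 1):* affected, by the factor in step 5.
- *Spearman correlations (Table 1, row 4):* unaffected. Multiplying by a positive constant leaves ranks unchanged.
- *Logistic regression (Table 1, rows 2 and 3):* unaffected as planned. Candidates are the variables significant in the one-factor analysis, and row 2 lists only demographic and clinical characteristics there. The DSES is not among them.
- *Sample size (section 2.4.1):* unaffected. It comes from a count of variables, 21 × 10 = 210 and 210 × 1.2 = 252, with no use of DSES scores.
- *Low, medium and high participation levels:* unaffected. They are cut on the SDM-Q-9.

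**The case against.** The best case on the other side accepts the arithmetic and disputes its weight. The fraction looks like a transposition slip in the article. Item count, coding and range determine the intended factor uniquely, and the range comes in the sentence right after the rule, so an attentive analyst would see that no patient can exceed 19.36. No DSES cut-offs are set, so nobody would be misclassified. The DSES is not among the interview sampling criteria named in section 2.5.1. The transform is fully reversible, and no item data are lost. All of this stands. It limits the severity, but it does not remove the error: the plan states a specific formula that contradicts its own range, and correct reporting should not depend on someone noticing.

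A reader might also infer more than the documents support:

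- *That regression coefficients would be wrong.* No DSES coefficient is planned in the logistic model as Table 1 lists it. Were one added, only its per-point unit would change; its p-value would not.
- *That the article names the DSES as its measure of perceived behavioral control.* It never says so expressly. Section 2.2 defines that construct through perceived resources, opportunities and obstacles. The confidence questions in the interview outline (Table 2) make the link reasonable, but it remains an inference.
- *That patients will be reported as having almost no confidence.* That follows only if the printed rule is applied literally and nobody notices the ceiling. The article shows no scoring code, so whether the slip has gone beyond the text is unknown.

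**Conclusion.** The error is real and follows from the article's own figures, with no outside source needed. As written, the rule has a ceiling of 19.36 where the article says 100. The size of the consequence, a factor of 5.17 on every reported DSES level, rests on one assumption: that the printed rule is used literally in scoring. Under that assumption the damage is confined to descriptive values, how they are read against the 0 to 100 anchors, and anything in the interview and integration stages that draws on them. No planned test, model, sample-size figure or participation category changes. This is a correction that should be made, but it does not threaten the study's inferences.

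**What to change.** In section 2.4.3, item (3), replace the multiplier 11/25 with 25/11, so that the total is the sum of the 11 items × 25/11. An equivalent wording that is harder to invert is the mean of the 11 items × 25. Then confirm that the scoring used in the SPSS analysis follows the corrected rule, with a simple check: all items at 0 must return 0 and all items at 4 must return 100.

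The cost is one text correction and one check of the scoring. Data collection does not change. If any totals have already been computed with 11/25, they can be recomputed from the item responses or multiplied by 625/121.

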
#### 2.4.4. Data Analysis

The questionnaire will be checked by two people, and scientific statistical methods will be used for rigorous statistical analysis. The quantitative data collected through interviews will be analyzed using SPSS26.0. Descriptive statistics will be used to present all the variables (Table 1). Mann–Whitney U-tests or multi-sample rank-sum tests will be used to analyze the differences between general information and the level of participation in SDM in patients with SCAD. The variables that are statistically significant after monofactor analysis will be used as independent variables, and participation in SDM by SCAD patients will be used as the dependent variable for conducting multiple logistic regression analyses. The Spearman correlation analysis will be used to describe the correlation between the variables in the TPB model and participation in SDM by SCAD patients. Two-tailed *p*-values will be adopted, and *p* < 0.05 will be considered statistically significant.

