### 2.4. Stage 1: Quantitative Study

#### 2.4.1. Sample

A convenience sampling method will be used to recruit participants. The study included 14 demographic and clinical characteristics and seven dimensions corresponding to five formative scales, with a total of 21 variables (Table 1). According to the sample estimation algorithm proposed by Kendall [24], the sample size is 10–20 times the number of variables, and the minimum sample size of this quantitative survey is 210. Moreover, considering 20% of the lost follow-up rate and invalid questionnaires, the final minimum sample size for the study is 252.

The inclusion criteria are as follows: (1) meets the diagnostic criteria of SCAD in the Guidelines for Diagnosis and Treatment of Stable Coronary Heart Disease [25]; (2) ≥18 years old; (3) signed informed consent.

The exclusion criteria are as follows: (1) patients with emergency admissions; (2) patients fully delegated to the family decision-maker; (3) patients with communication disorders; (4) diagnosed with mental illnesses; (5) pregnant patients; (6) patients with severe cardiac, liver, or renal dysfunction or critical illness.

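### Logistic regression is fixed for a 0–100 participation score: the score must be grouped, which loses power, and the participants-per-variable sizing does not carry over to such a model

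*Protocol article*

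**What the plan says.** **Outcome.** Section 2.4.3, item (5), describes the SDM-Q-9 as a graded score: "The initial author suggested that the original score × 20/9 be converted to 0–100 points for easy comparison", and "Higher scores indicate a greater degree of patient participation in SDM". It also gives three bands: "The total scores of 0–33, 34–66, and 67 and above indicated low, medium, and high levels of patient participation in shared decision making".

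**Model.** Section 2.4.4 states that "participation in SDM by SCAD patients will be used as the dependent variable for conducting multiple logistic regression analyses". Table 1 repeats this. Neither place says whether the model is binary, ordinal or multinomial, how the score would be cut, or why the score is not modelled directly. Only variables significant in the single-factor analysis enter. Table 1 lists 17 demographic and clinical characteristics for that analysis; the theory-of-planned-behavior scales appear only under Spearman correlation.

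**Sample size.** Section 2.4.1 counts total participants per variable: "The study included 14 demographic and clinical characteristics and seven dimensions corresponding to five formative scales, with a total of 21 variables"; "the sample size is 10–20 times the number of variables, and the minimum sample size of this quantitative survey is 210"; "considering 20% of the lost follow-up rate and invalid questionnaires, the final minimum sample size for the study is 252". It does not mention category sizes.

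**The concern.** A logistic model needs a categorical outcome. With only three bands defined, the natural way to carry out the plan is to group a score that was collected on a finer scale. Patients at the two ends of one band then count as identical, and patients just either side of a cut count as different. Power to detect influencing factors falls, and finding those factors is one of the three research questions in Section 2.1.

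The sample size has a related gap. Ten participants per variable is a rule of thumb about total numbers. In a binary or multinomial logistic model, stability depends on the number of patients in the smallest outcome category. If that category is small, odds ratios become unstable, tend to be biased away from 1, or cannot be estimated.

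**Working it through.** **1. The plan's own figures.** 10 × 21 = 210. 210 × 1.20 = 252. Both reproduce, and 210/21 = 10 participants per variable, so the stated rule is met. If 20% of 252 are lost, 252 × 0.80 = 201.6, or 201 evaluable.

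**2. Power lost by grouping.** The documents give no effect size and no score distribution. Assumed: n = 201, roughly normal score with mean 60 and SD 20, one predictor with correlation r = 0.20, two-sided 5%.

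- Cuts: (33.5 − 60)/20 = −1.325 and (66.5 − 60)/20 = 0.325.
- Shares: about 9% low, 53% medium, 37% high.
- Normal densities at the cuts: 0.166 and 0.378.
- Information kept relative to the score is the sum over categories of (difference in density at its two limits)² / share:
  - three ordered levels: 0.166²/0.093 + (0.166 − 0.378)²/0.535 + 0.378²/0.373 ≈ 0.77
  - high versus rest: 0.378²/(0.373 × 0.627) ≈ 0.61
  - low versus rest: 0.166²/(0.093 × 0.907) ≈ 0.33
- Approximate power = Φ(r√n × √information − 1.96), with r√n = 0.20 × √201 = 2.835.

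| Outcome used | Information kept | Power, formula | Power, simulation |
|---|---|---|---|
| 0–100 score | 1.00 | 81% | 82–83% |
| Three ordered levels | 0.77 | 70% | 68–69% |
| High versus rest | 0.61 | 60% | 60–61% |
| Low versus rest | 0.33 | 37% | 33–38% |

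The simulations used the same inputs.

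*Range (same formula, n = 201).* Powers are in the order score, three levels, high versus rest, low versus rest. At mean 60, r = 0.15 gives 57, 46, 38 and 23%; r = 0.30 gives 99, 96, 91 and 68%. At r = 0.20, a mean of 50 gives 81, 71, 51 and 51%; a mean of 70 gives 81, 66, 61 and 22%. The size of the loss varies, but the score has the highest power in every case.

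**3. What 210 patients support in a binary or multinomial model.** Events = 210 × share of the smallest category. The shares are assumed, since the documents give none.

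| Smallest category | Events | Parameters at 10 events each | Events per variable, all 17 characteristics |
|---|---|---|---|
| 20% | 42 | 4 | 42/17 = 2.5 |
| 30% | 63 | 6 | 63/17 = 3.7 |
| 50% | 105 | 10 | 105/17 = 6.2 |

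The last column is the case in which every characteristic passes the screen. Table 1 sends nine of the 17 to multi-sample tests, so these have at least three levels. Coded as dummies, the 17 need at least 8 + 9 × 2 = 26 parameters.

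**4. Ordinal reading.** For a three-level ordinal model the effective size is N × (1 − Σp³). Equal thirds give 210 × 0.889 = 187; a 10/30/60 split gives 210 × 0.756 = 159. The limit is then much milder: 8.9 and 7.6 per variable for 21 variables.

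**5. Dependence on the cuts.** Section 2.4.3 scores nine items 1 to 6 and multiplies by 20/9, which gives 9 × 20/9 = 20 to 54 × 20/9 = 120, not 0–100. A constant shift of 20 points leaves linear slopes unchanged, but it moves patients between bands. Under the assumptions above, the high band would go from about 37% to about 75% and the low band from about 9% to about 1%.

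**The case against.** A reader might infer that the study breaks its own sizing rule. It does not: that rule counts participants, and it is met exactly. Ten events per variable is a different rule that the article never adopts.

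A reader might also infer that the model is certain to be overloaded. The documents do not support that either. Only screened variables enter, and neither the number retained nor the category shares are known. With a 30% smallest category, six single-parameter variables give 63/6 = 10.5 events each. An ordinal model on the three levels, arguably the natural reading of ordered bands, is hardly limited in this way and costs about 13 percentage points of power in the base case, far less than low versus rest.

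The grouping itself is inferred, and an article may leave model details to a fuller plan. The bands also have a use: they guide interview selection, so a regression on the same levels would link the two phases. Nor is it shown that the analysis steps use different scales, since rank tests and Spearman correlation can also be run on ordered levels.

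These points limit the claim without removing it. The article does fix a logistic model for a scored outcome and gives no reason, and even the ordinal reading loses power. Only a proportional-odds model on the full score would avoid grouping, and the text does not mention one.

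**Conclusion.** The point holds in a limited form. Naming logistic regression for the SDM-Q-9 score implies, in practice, grouping it, at an avoidable cost of about 13 percentage points of power with three ordered levels and over 40 for low versus rest. Those sizes rest on an assumed correlation of 0.20, mean 60, SD 20 and 201 evaluable patients.

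The sample size is arithmetically consistent with its own rule, but it gives no assurance for a binary or multinomial logistic model. Whether a shortfall occurs depends on how many parameters are retained and on the smallest category, and the documents give neither.

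**What to change.** In Section 2.4.4 and Table 1, make multiple linear regression of the SDM-Q-9 score with robust standard errors the main model. If ceiling effects are marked, use a proportional-odds model on the full ordered score instead. Keep low, medium and high for description and for selecting interviewees. If odds ratios are wanted, keep a logistic model on the three ordered levels as a secondary analysis, with its type and cuts stated. The item scoring and the 0–100 range should be reconciled first, since any banded analysis depends on them.

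The cost is a change of wording; no new data or patients are needed. The downside is that main results are in scale points instead of odds ratios (the proportional-odds alternative would still give odds ratios).

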### 2.2. Theoretical Framework

The theory of planned behavior (TBP) framework was adopted in this study (Figure 1). According to the TPB, intention is influenced by attitude, subjective norm, and perceived behavioral control, while behavior is influenced by both intention and perceived behavioral control [23]. Attitude is a comprehensive assessment of performing a certain behavior. In this study are views on the benefits, disadvantages, and outcomes of participating in SDM behavior.

Subjective norm refers to the social pressure exerted by significant others for someone to engage in a particular behavior and their level of support for that behavior. In this study, it was defined as the degree to which SCAD patients felt the pressure of their significant other and the support they provided when deciding whether to engage in SDM behavior.

Perceived behavioral control measures how a person perceives the ease or difficulty in performing a behavior. Perceived behavioral control increases with individuals’ perceptions of having greater resources and opportunities available to them, along with fewer perceived obstacles. In this study, it is defined as the resources, opportunities, and obstacles that SCAD patients perceive when they participate in SDM behavior.

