**Figure 3 healthcare-12-01883-f003:**
[figure not shown]
Gantt chart for this mixed method study.

**Table 1 healthcare-12-01883-t001:** Statistical test information table.

Statistical Test Information Table			
Num	Tests	Variables	Type of Information
1	descriptive statistics	demographic and clinical characteristics, participation in SDM, patient attitudes, decision self-efficacy, intention, and social support	Frequency, percentage; Mean ± SD or M (P_25_, P_75_) (normality or not)
2	monofactor analysis	sex, BMI, ethnicity, place of residence, working conditions, medical payment method, stent implantation or not, and the first time to be hospitalized for SCAD or not	Mann–Whitney U-tests
		age, marital status, education level, average annual household income, drinking status, smoking status, duration of illness, severity of angina, and number of diseased coronary arteries	multi-sample rank-sum tests
3	multiple logistic regression analyses	Variables that are statistically significant after monofactor analysis	independent variables
		participation in SDM	dependent variable
4	Spearman correlation analysis	participation in SDM (Single dimension)	
		patient attitudes (Single dimension)	
		decision self-efficacy (Single dimension)	
		intention (Single dimension)	
		social support (friends support, family support, and significant other support)	

Demographic and clinical characteristics: sex, BMI, ethnicity, place of residence, working conditions, medical payment method, stent implantation or not, and the first time to be hospitalized for SCAD or not; age, marital status, education level, average annual household income, drinking status, smoking status, duration of illness, severity of angina, and number of diseased coronary arteries.

**Table 2 healthcare-12-01883-t002:** Semi-structured Interview Outline.

Opening remarks	I appreciate your interest in this study. I will ask you some questions about your involvement in SDM during this hospitalization. Your responses will be recorded, but your identity will remain confidential.	

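### As written, no TPB score can enter the logistic regression, so the plan yields no adjusted association between any TPB construct and SDM participation

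*Protocol article*

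**What the plan says.** Section 2.2 sets out the framework: "intention is influenced by attitude, subjective norm, and perceived behavioral control, while behavior is influenced by both intention and perceived behavioral control". Section 2.1 asks, as its third question, what influences patients' participation in SDM.

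Section 2.4.4 and Table 1 then assign each variable to an analysis:

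- **Monofactor step.** Rank tests "will be used to analyze the differences between general information and the level of participation in SDM in patients with SCAD". Section 2.4.3 uses the term general information for the demographic and clinical questionnaire. Table 1, row 2, gives the Mann–Whitney list, which begins "sex, BMI, ethnicity, place of residence, working conditions, medical payment method, stent implantation or not" and ends with first hospitalization for SCAD. It also gives the multi-sample list: "age, marital status, education level, average annual household income, drinking status, smoking status, duration of illness, severity of angina, and number of diseased coronary arteries".
- **Regression.** "The variables that are statistically significant after monofactor analysis will be used as independent variables". Table 1, row 3, gives the same entry rule: "Variables that are statistically significant after monofactor analysis".
- **TPB scales.** "The Spearman correlation analysis will be used to describe the correlation between the variables in the TPB model and participation in SDM". In Table 1 these scales appear under descriptive statistics (row 1) and Spearman correlation (row 4), and nowhere else.

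Section 2.4.1 bases the sample size on 14 characteristics plus "seven dimensions corresponding to five formative scales, with a total of 21 variables".

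**The concern.** The only multivariable model in the plan is reserved for background characteristics, while the constructs that motivate the study get pairwise coefficients. Attitude, self-efficacy, intention and perceived support are likely to be related to one another and to age, education and income. An unadjusted coefficient cannot separate a construct's own relation to participation from what it shares with those variables.

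This bears on the third research question. The quantitative results are to guide revision of the interview outline (sections 2.5.2 and 2.5.3), to be combined with the interview themes in a joint display framed by TPB (section 2.6), and to inform later interventions (sections 1 and 3.1). On the TPB side, those uses would rest entirely on unadjusted correlations.

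**Working it through.** **1. The sample-size figure.** Section 2.4.1 takes 10 per variable, the lower end of its 10–20 range: 10 × 21 = 210. Adding 20% gives 210 × 1.20 = 252, which reproduces the stated minimum.

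**2. What the seven dimensions are.** Table 1, row 4, shows participation (1), attitudes (1), self-efficacy (1), intention (1) and social support (3: friends, family, significant other): 1 + 1 + 1 + 1 + 3 = 7. One is the outcome and six are TPB scores. The article does not match each scale to a construct in so many words. Section 2.4.4 refers to the variables in the TPB model, and row 4 lists these scales.

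**3. Tracing each variable to an analysis.**

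| Variables | Monofactor (row 2) | Eligible for regression (row 3) | Spearman (row 4) |
|---|---|---|---|
| 8 characteristics, Mann–Whitney | yes | yes, if significant | no |
| 9 characteristics, multi-sample rank-sum | yes | yes, if significant | no |
| 6 TPB scores | no | no | yes |

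Eligible variables: 8 + 9 = 17, of which 0 are TPB scores. All six TPB scores stop at Spearman. (Section 2.4.1 says 14 characteristics, but section 2.4.3 and Table 1 list 17. That mismatch is a separate matter; the larger count is used here.)

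**4. What the planned output contains.** Associations of a TPB score with participation adjusted for characteristics: none. Adjusted for other TPB scores: none. Models with intention as outcome: none.

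**5. Whether the fix fits the protocol's own rule of 10 per variable.**

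- Total social support score (section 2.4.3 defines one): 17 + 4 = 21 predictors, and 10 × 21 = 210 analysable. This equals the present minimum.
- Three support subscales instead: 17 + 6 = 23 predictors, and 10 × 23 = 230 analysable. Recruitment would be 230 × 1.20 = 276, or 230 / 0.80 = 287.5, rounded up to 288. Both exceed 252.

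Two cautions. If a full 20% of 252 are lost, 252 × 0.80 = 201.6 remain, slightly under 210; that shortfall is already in the plan and does not come from the fix. The rule also counts variables rather than coefficients, so a characteristic with several categories uses more than one coefficient.

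**The case against.** **The text may simply be loose.** Table 1, row 3, does not name the regression variables, and counting the scales in the sample size suggests that they may have been meant for the model. This is a fair point about intent. It does not change what is written: the monofactor list is given in full without the scales, and Spearman is a separate row. If inclusion was intended, the text still needs correcting.

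**Spearman is offered only as description, and the aims are exploratory.** True. The article does not promise to test TPB paths, and the first two research questions are unaffected. The interviews also explore each TPB domain, but 10–20 interviews cannot supply adjusted estimates.

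**A reader might infer that the Spearman results would be false leads.** For example, attitude could correlate with participation and yet show nothing once intention is adjusted for. The documents do not support that inference. Under section 2.2 attitude works through intention, so in that case attitude is a genuine indirect factor and Spearman has detected it. The null adjusted result would come from conditioning on a mediator.

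**A reader might also infer that the characteristics-only regression is invalid.** It is not. If age or education act partly through attitude or self-efficacy, leaving those scales out estimates the total association, which is a legitimate answer to the third question.

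**Conclusion.** The point holds in a limited form. The plan gives no association between any TPB construct and SDM participation that is adjusted for patient characteristics or for the other constructs: 0 of 17 eligible predictors are TPB scores, and 6 of 6 TPB scores receive only pairwise Spearman correlations. This sits badly with a TPB-based study that asks for influencing factors and counts these scales in its sample size.

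The conclusion rests on reading section 2.4.4 and Table 1 as they stand. The size of any confounding cannot be stated, because the documents give no correlations between the TPB scores and age, education or one another.

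The finding does not extend to mediation. A reader might want indirect effects through intention, but section 2.4.2 has a single survey one or two days before discharge, and the participation being rated belongs to the treatment already received. The data cannot establish that intention came before behavior.

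**What to change.** Amend section 2.4.4 and Table 1, row 3, as follows:

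- Enter attitude, decision self-efficacy, intention and social support (total score) in the multivariable model of participation, regardless of univariable p-value, together with the demographic and clinical covariates.
- Report the model with and without intention, because TPB places intention between attitude or norm and behavior. Without it, the other coefficients include whatever they share with intention; with it, they do not.
- Keep row 4 (Spearman) as description.
- Optionally, add a regression of intention on attitude, social support and self-efficacy.
- State that all results are cross-sectional associations and that no mediation claim will be made.
- State the direction of the intention score, since section 2.4.3 says that a lower score means greater intention.

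The cost is a few lines of text and one or two further models in software already named, using scales already being collected. The downside is a larger model and somewhat lower precision per coefficient. Using the three support subscales in place of the total would raise the requirement under the protocol's own rule from 210 to 230 analysable patients, so that choice should be stated in advance.
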